### Exercise therapy

The exercise therapy content is based on recommendations for preoperative exercise therapy.^28^ The exercise protocol follows a standardised structure but is individually customised for each patient. It is divided into four sections with different exercise focus (warm-up, strengthening, balance and ROM exercises), and each exercise within each section has three difficulty levels (table 2). The content is designed and dosed to promote maximal strength development in multijoint strength exercises, muscle hypertrophy in single-joint strength exercises, improved balance and increased joint ROM.^29^,^31^

**Table 2 T2:** Exercise therapy content

Exercise type		Exercise options	Difficulty level	Dosage, set × reps/time	Effort/intensity
Warm-up exercises	1	Stationary bike Seated bike Cross-trainer	N/A	10 min	RPE 11–12
Strengthening exercises	2	Bilateral leg press (full ROM) Bilateral leg press (partial ROM) Unilateral leg press (full ROM)	Main option Easier Harder	3×6 (primary) 3×8 (secondary) 3×10 (tertiary)	RPE 17–18
	3	Supine unilateral hip bridges Supine bilateral hip bridges Supine unilateral hip thrusts	Main option Easier Harder	3×6 (primary) 3×8 (secondary) 3×10 (tertiary)	RPE 17–18
	4	Bilateral seated leg extensions (machine) Unilateral seated leg extensions with ankle weights Unilateral seated leg extensions (machine)	Main option Easier Harder	3×12 (primary) 3×13 (secondary) 3×14 (tertiary)	RPE 17–18
	5	Bilateral seated leg curls (machine) Unilateral seated leg curls with resistance band Unilateral seated leg curls (machine)	Main option Easier Harder	3×12 (primary) 3×13 (secondary) 3×14 (tertiary)	RPE 17–18
	6	Standing bilateral calf raises Seated unilateral calf raises with weights Standing unilateral calf raises	Main option Easier Harder	3×12 (primary) 3×13 (secondary) 3×14 (tertiary)	RPE 17–18
Balance exercise	7	Static unilateral balance, level ground, no hand support Static unilateral balance, level ground with hand support Static unilateral balance, unstable surface, no support	Main option Easier Harder	3×30 s	Ability to maintain balance
Range of motion exercises	8	Supine active flexion slides Seated active flexion slides Supine active flexion slides with end-range assistance	Main option Easier Harder	5×5 s	Pain NRS ≤5 (0–10)
	9	Supine active knee extensions, heel elevated Supine active knee extensions Supine active knee extensions, heel elevated, extra weight	Main option Easier Harder	5×5 s	Pain NRS ≤5 (0–10)

N/A, not applicable; NRS, numerical rating scale; ROM, range of motion; RPE, rate of perceived exertion.

The Borg scale for rating of perceived exertion (RPE)^32^ is used to monitor exercise effort in strengthening exercises, with an RPE of 17–18 as the target. Pain response during knee ROM and strengthening exercises is monitored using a numerical rating scale (NRS) of 0–10.^33^,^36^ Pain intensity is allowed to increase by up to five points from the start of the exercise and should subsequently decrease by at least two points before initiating the next set or exercise. In balance exercises, the ability to maintain balance during a set is used to monitor effort.

The rest period between sets or exercises is not standardised. Patients are instructed to rest for as long as needed for fatigue and/or pain to settle sufficiently (as described above) before starting the next set or exercise. Based on this, rest periods are typically between 1 and 3 min.

#### Exercise progression

Exercises are progressed when patients can complete the prescribed dosage without an unacceptable pain response, as described in the previous section.^33^,^36^ In strengthening exercises, linear progression of exercise intensity by the smallest possible increment in each exercise is the primary progression method, but if linear progression is not suitable, progression is achieved by increasing volume through additional repetitions (3×6 → 3×8 → 3×10 or 3×12 → 3×13 → 3×14 → 3×15), adding exercises or increasing exercise difficulty. In ROM exercises, progression is mainly achieved by increasing the exercise difficulty level or by increasing end-range stretching amplitude (allowed pain intensity NRS ≥5). In balance exercises, when the patient can maintain balance with ease, exercises are progressed by increasing exercise difficulty (table 2).

#### Exercise individualisation

The exercises are individualised primarily by selecting the exercise difficulty level (easier, main or harder option) but can also be tailored by adjusting the total number of exercises in the protocol (minimum four exercises, maximum nine exercises, including warm-up) (table 2).

An individual assessment of previous exercise habits is conducted for each patient at baseline, before designing the initial exercise therapy protocol. Patients are asked about their level of physical activity, exercise and sedentary time over the previous month, and whether they currently perform any exercises targeting the knee or lower extremities. Patients who report regularly performing lower extremity strengthening exercises (at least once per week) can begin at a higher level (harder exercise options or more exercises) compared with patients who do not engage in regular lower extremity strengthening exercises.

#### Knee health monitoring and training load adjustments

Before each session, patients assess their overall knee health using the Single Assessment Numerical Evaluation (SANE) score and record it in the exercise protocol. The SANE score is a patient-reported rating scale in which respondents assess their knee health on a 0–100 scale, with 100 representing full health and 0 the worst possible health.^37^ Patients answer the question, ‘How do you rate your overall knee health today?’ The SANE score has been validated against commonly used PROMs (patient-reported outcome measures) and is suitable for assessing overall knee health in daily clinical practice for patients undergoing TKR.^38^

The SANE assessments are monitored throughout the entire intervention. Training loads are adjusted if patients report worsening knee health over three consecutive sessions. Load reduction is primarily achieved by decreasing intensity, but volume or exercise difficulty may be reduced if lowering intensity is not appropriate. Conversely, if patients report stable or improved knee health over time, training loads are progressed as planned.

#### Patient education

The patient education consists of individual conversations between the physiotherapist and the patient on various topics, selected based on consensus in previous literature.^28^ The topics are presented in box 1. Conversations take place during exercise sessions, either during the warm-up, between sets or at the end of the session, and may involve one-on-one discussions or multiple patients at the same time. Conversations typically begin with questions posed by the physiotherapist, for example, ‘What are your thoughts/expectations of…?’ or with questions from the patients. The conversation format is not standardised but is adapted according to the situation.

Box 1Education topicsPurpose of prehabilitation.The pain monitoring model.Pain and swelling with exercise and load.Postoperative course of events.Postoperative rehabilitation.Postoperative pain and swelling.Expectations of future function/ability.Expectations of future activities/activity level.Other.

The aim of the conversation is not to convince or instruct patients on what their expectations should be, but to create a nuanced and realistic understanding of what to expect during recovery after TKR and to individually tailor the content to each patient. All education topics are discussed with each patient on at least two occasions. Patients are encouraged to reflect on the conversations until the next session and to ask follow-up questions if needed. If the same ‘other topic’ arises in conversations with multiple patients, it is considered a main topic and will be included in discussions with all patients going forward.

### Standard care

Before surgery, standard care consists of self-care and a single, standardised 1.5-hour preoperative education session, delivered approximately 2–3 weeks before surgery. General oral and written information is provided regarding preparations for surgery (eg, preparing the home environment), events during the hospital stay and initial postoperative rehabilitation. No specific preoperative exercise advice is given. The standardised preoperative education session is delivered by healthcare staff (physiotherapist, occupational therapist, nurse) who are not involved in the present trial.

During the hospital stay (1–2 overnights) after surgery, all patients are instructed in and begin a standardised home-based postoperative rehabilitation protocol. Instruction is provided by physiotherapists at the orthopaedic clinic, with follow-up conducted by a primary care physiotherapist. All patients are scheduled for a 6-week post-surgery assessment by a physiotherapist at the orthopaedic clinic. Following this assessment, patients in both groups return to their primary care physiotherapist and continue rehabilitation based on their individual goals for as long as necessary. No further follow-up assessments are scheduled at the orthopaedic clinic.

### Data collection and blinding

A questionnaire covering patient demographics, lifestyle behaviours, expectations and PROMs is mailed to patients, completed and brought to the baseline assessment, where objective function measures are conducted. At the baseline assessment, a triaxial accelerometer (activPAL) is attached to the front of the thigh of the affected leg and worn 24 hours a day for 7 days. The accelerometer is then returned to the trial coordinator using a pre-paid reply envelope.

Follow-up assessments are conducted immediately after the 8-week intervention and at 6, 12 and 52 weeks post-surgery. Waiting times for surgery will vary between patients, and if more than 4 weeks elapse between the post-intervention follow-up and surgery, an additional follow-up assessment will be scheduled approximately 1 week before surgery.

PROMs are collected at every follow-up assessment. Measures of objective function are conducted at the 8-week follow-up, 1 week before surgery and 6 weeks after surgery. The activPAL accelerometer is worn 24 hours a day for 7 days immediately after the 8-week follow-up and at the 12-week and 52-week postoperative follow-up assessments.

Outcome data are collected locally at each participating centre. All PROMs in the trial are administered via paper surveys. Measures of objective function are assessed by a physiotherapist blinded to group allocation. Physiotherapists performing these assessments are trained on two occasions before participating in the trial, during which pilot measurements of objective outcome measures are conducted under the supervision of the trial coordinator. The assessors also participate in monthly meetings with the trial coordinator throughout the trial to address potential issues.

Patients are not blinded to group allocation but are not informed of the trial hypothesis until data collection is complete. An overview of the trial timeline and data collection is provided in figure 1 and table 3.

**Table 3 T3:** Data collection/outcome measures

Data collection time points	Baseline	8-week follow-up	1-week preop follow-up (if necessary)	6-week postop follow-up	12-week postop follow-up	52-week postop follow-up
Demographics, lifestyle behaviours, expectations, etc	X					
PROMs						
FJS-12	X	X	X	X	X	**X**
Satisfaction						X
Mod-PEI-2	X	X	X	**X**	X	X
KOOS	X	X	X	X	X	X
IPAQ-sf	X	X	X	X	X	X
EQ5D-3L	X	X	X	X	X	X
Objective function						
Isometric quadriceps strength	X	X	X	**X**		
Active knee ROM	X	X	X	**X**		
30s CST	X	X	X	**X**		
activPAL accelerometer	X	X			X	X

Bold crosses are considered main outcome time points.

EQ5D-3L, EuroQol 5 Dimension 3 Levels; FJS-12, Forgotten Joint Score-12; IPAQ-sf, International Physical Activity Questionnaire-short form; KOOS, Knee injury and Osteoarthritis Outcome Score; Mod-PEI-2, modified Patient Enablement Instrument 2; postop, postoperation; preop, preoperation; ROM, range of motion; 30s CST, 30 second Chair to Stand-Test; w, week.

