### Patient recruitment and inclusion/exclusion criteria

Participating centres contribute to patient recruitment using a stepwise approach, with one centre initiating recruitment first and the other following in the second stage. All patients referred to an orthopaedic surgeon at the participating hospitals for assessment of the need for TKR are screened for eligibility and receive written information about the trial by post from an administrator before the appointment. Eligible patients (table 1) receive additional oral information and are invited to participate in the trial by a nurse involved in the appointment. The nurse obtains signed informed consent (online supplemental file 1) and delivers it to the trial coordinator (lead author). Time for consideration is offered if needed. An appointment for baseline measures and randomisation is scheduled by the trial coordinator. A visual representation of the trial timeline is shown in figure 1.

**Table 1 T1:** Inclusion and exclusion criteria

Inclusion criteria	Exclusion criteria
40–85 years at the time of surgery decision	Previous knee replacement in the other knee
Awaiting primary unilateral total knee replacement	Other reason than knee OA as the primary reason for surgery
Knee OA being the primary reason for surgery	Impaired cognitive function
Reside within 60 min travel time to the site of the intervention	Not fluent in written and spoken Swedish
	Chronic illness or disability, etc hindering full participation in the intervention

OA, osteoarthritis.

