### Randomisation

Patients are randomised using opaque, concealed envelopes and stratified by age (≤67 years, >67 years) with a 1:1 allocation ratio, based on computer-generated random number sequences, into the intervention group, comprising prehabilitation in addition to standard care (SC+P), or the control group, consisting of standard care only (SC). The computer-generated random number envelope sequences were created by a person not otherwise involved in the trial. Allocation is performed by the trial coordinator immediately after the baseline assessment. The trial coordinator did not have access to the randomisation lists before allocation.

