### Analysis plan

All analyses will be performed using IBM SPSS Statistics software, V.29, applying intention-to-treat and per-protocol approaches with an α-level of 0.05. Demographic data will be presented as mean or median with SD or IQR for quantitative variables, and as frequencies and percentages for categorical variables.

Depending on measurement scale and distribution, differences between groups at baseline and for primary and secondary outcomes at each follow-up assessment will be analysed using independent samples t-tests or non-parametric equivalent tests. Longitudinal changes within groups from baseline to follow-up time points will be analysed using linear mixed models or generalised linear models, with baseline measurements included as covariates. Multiple linear regression and logistic regression will be used to analyse predictor variables for the primary outcomes (FJS-12 and Mod-PEI-2). Furthermore, analyses of primary and secondary outcomes will be adjusted, if necessary, for differences in intervention delivery and adherence, duration of participation, surgical procedures and postoperative physiotherapy care.

Multiple analyses will be performed using α-level adjustment methods, such as the Bonferroni method. In the intention-to-treat analysis, a sensitivity analysis will be performed to quantify the magnitude of missing data from patients lost to follow-up. Appropriate statistical methods will be used to account for missing data in the analysis, depending on the characteristics of the missing data. If there is extensive missing data, a second table of baseline characteristics will be presented only for patients included in the final analysis. The proportion of missing outcomes per group, characteristics of patients with missing data and possible reasons for missing outcome data will be presented.

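### The activPAL week labelled Baseline is recorded after allocation in unblinded patients, so it can bias any activPAL result that uses it as a reference or covariate

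*Protocol article*

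**What the plan says.** Four statements in the protocol article fix the order of events.

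- Patient recruitment and inclusion/exclusion criteria: one visit serves both purposes. "An appointment for baseline measures and randomisation is scheduled by the trial coordinator".
- Data collection and blinding: "At the baseline assessment, a triaxial accelerometer (activPAL) is attached to the front of the thigh of the affected leg". It is worn round the clock for 7 days, and "The accelerometer is then returned to the trial coordinator using a pre-paid reply envelope".
- Randomisation: "Allocation is performed by the trial coordinator immediately after the baseline assessment".
- Data collection and blinding, on who knows the arm: "Patients are not blinded to group allocation but are not informed of the trial hypothesis until data collection is complete".

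Table 3 enters this first activPAL recording in the Baseline column, followed by recordings at 8 weeks and at 12 and 52 weeks after surgery.

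The Analysis plan section tests group differences at baseline and at each follow-up with t-tests or non-parametric equivalents. It analyses within-group longitudinal change with mixed or generalised linear models, "with baseline measurements included as covariates". It makes no exception for activPAL.

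**The concern.** A baseline value may serve as a covariate or as the starting point for change because randomisation cannot have influenced it. Here the recording runs after allocation, in patients who know their arm, and it measures daily activity, which an exercise programme and the knowledge of receiving or not receiving it could change. SC+P patients may become more active at once, and SC patients may react to their allocation in either direction.

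Three uses of the recording are exposed:

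- The baseline comparison between arms, where an early effect of allocation would look like chance imbalance.
- Change from baseline, within each arm and contrasted between arms.
- Any model that adjusts for activPAL baseline.

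The Introduction presents the preoperative and postoperative activPAL data as novel, so a sound preoperative reference matters even though this is a secondary outcome. No later analysis can recreate a pre-allocation recording.

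**Working it through.** **Timing.** Take the baseline visit as day 0.

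- Questionnaires, including IPAQ-SF: completed at home and brought to the visit, so before allocation.
- Objective function tests: done at the visit, before allocation.
- Allocation: day 0, directly after the assessment.
- activPAL wear: day 0 to day 7, so essentially all after allocation.

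The baseline assessment cannot be read as including the wear week. The text describes it as a visit to which forms are brought and at which tests are done, and the device comes back by post. No run-in week and no delayed opening of the envelope is described. The problem is therefore specific to activPAL.

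**Patients exposed.** The target of 110 reproduces: a two-sided 5% t-test (sidedness assumed) at effect size 0.61 with 80% power needs 44 per arm, 44 / 0.8 = 55, and 2 × 55 = 110. The section on trial status says activPAL was added after the first 22 patients, so at most 110 − 22 = 88 patients are recorded this way. The point does not otherwise depend on the sample size.

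**Bias.** Let x be the SC+P minus SC shift in week-1 activity caused by allocation, b the within-arm slope of follow-up on this recording, and δ the true difference at follow-up. Assume the shift is the same for all patients within an arm. Then:

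- Follow-up values only: expected estimate δ.
- Change score: δ − x.
- Adjusted for the recording: δ − b·x.

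Within one arm, change is off by that arm's own shift.

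The documents give no value for x, b or δ. For illustration, in SD units with equal variances (so b equals the correlation), assume δ = 0.30 and b = 0.5 or 0.7:

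| x | Adjusted, b = 0.5 | Adjusted, b = 0.7 | Change score | Follow-up only |
|---|---|---|---|---|
| −0.1 | 0.30 + 0.05 = 0.35 | 0.30 + 0.07 = 0.37 | 0.40 | 0.30 |
| 0 | 0.30 | 0.30 | 0.30 | 0.30 |
| 0.1 | 0.30 − 0.05 = 0.25 | 0.30 − 0.07 = 0.23 | 0.20 | 0.30 |
| 0.2 | 0.30 − 0.10 = 0.20 | 0.30 − 0.14 = 0.16 | 0.10 | 0.30 |
| 0.3 | 0.30 − 0.15 = 0.15 | 0.30 − 0.21 = 0.09 | 0.00 | 0.30 |

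A simulation of 400,000 patients per setting agreed with the rows for x from 0 to 0.3 to within 0.005. The row for −0.1 comes from the formula alone.

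**Which planned analyses use the recording.** The between-group tests at follow-up have no baseline term, and the further adjustments listed in the Analysis plan (delivery and adherence, duration, surgery, physiotherapy) do not include one. The covariate wording belongs to the within-group longitudinal models. The Abstract, however, names t-tests and these models together for between-group and within-group differences, so a between-arm contrast drawn from the models is not ruled out.

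**The case against.** The order of events is hard to dispute. The case against concerns the consequence.

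- **The main activPAL comparison does not use baseline.** This stands. A reader might infer that the week-1 shift is subtracted from the trial's planned treatment effect on activity. The Analysis plan does not support that, because its stated between-group tests compare follow-up values alone.
- **Size and direction are unknown.** This stands. The shift may be zero. The text does not give the interval from allocation to the first session, and the timeline figure is not available here, so one cannot claim that sessions fall inside the wear week. Even if they did, two sessions of about 1 hour are roughly 2 of 7 × 24 = 168 recorded hours. That fraction does not settle the matter, since activity outside sessions can also change and a small part of the week may still be a notable part of a patient's active time.
- **Patients are not told the hypothesis.** This gives some protection against reactive behaviour, but they still know their arm.
- **88 patients.** A reader might take this as 88 patients with distorted data. It is only a ceiling on those exposed to the procedure.
- **Limited importance.** activPAL is a secondary outcome, has no main time point marked in Table 3 and is not in the stated aim. No primary conclusion is touched.
- **Costs of changing course.** Recruitment began in February 2024, so moving allocation now yields activPAL baselines with two meanings. IPAQ-SF is also a weak substitute covariate: the section on physical activity and sedentary habits says it under-records low-intensity activity and sedentary time and over-records higher-intensity activity. Both objections are fair and shape the fix.

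**Conclusion.** The concern holds in a limited form. The text establishes that the activPAL recording labelled Baseline is essentially post-allocation, in patients who know their arm. It can bias the activPAL baseline comparison, change-from-baseline results and baseline-adjusted models: by x for a between-arm change-score contrast, and by b·x for an adjusted one (50% to 70% of x if b is 0.5 to 0.7, which is an assumption). Whether it does so, and in which direction, cannot be known from the documents.

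The planned between-group tests at each follow-up are unaffected. So are FJS-12, Mod-PEI-2, the other questionnaires and the objective function tests, whose baselines precede allocation. A correction is worth making because it is cheap and recruitment is expected to run throughout 2026.

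**What to change.** **Patients already enrolled.** Label the recording as week 1 after allocation in Table 3 and in reports. Do not use it as a covariate or as the reference for change, and do not present it as a test of baseline balance. Compare follow-up activPAL between arms either without it, as the Analysis plan already allows, or adjusted for variables fixed before allocation: age stratum, centre and baseline IPAQ-SF, with the known limits of IPAQ-SF stated. This costs only a wording change and possibly some precision.

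**Patients still to be enrolled, where feasible.** Attach the device at the baseline visit, but open the envelope and inform the patient only after the 7-day wear has ended. Then x = 0 by design, concealment is kept and the sample size does not change. The cost is a protocol amendment, about one week's delay to allocation, one extra contact per patient and a small risk of withdrawal in that week. Because this alters the allocation step for every outcome, the sponsor may reasonably judge that the analysis change alone is enough.

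If both procedures occur, flag each activPAL recording as made before or after allocation and do not pool them as one baseline.
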